### Trial objectives

The objectives of this trial are as follows:
To verify the efficacy of fascial-point acupuncture in relieving hand spasm after stroke, and to improve the limb function and daily living ability of patientsTo provide more evidence for the clinical application of this therapy in the future

## Methods/design

### Trial design

This is a multicenter, prospective, randomized controlled trial supported by the Shanghai Science and Technology Commission. The trial will be carried out jointly by the Seventh People’s Hospital affiliated to Shanghai University of Traditional Chinese Medicine and two other hospitals in Shanghai. Patients meeting the pre-defined criteria will be randomly divided into three groups: an acupuncture group undergoing fascial-point acupuncture with routine rehabilitation treatment, a sham acupuncture group undergoing sham acupuncture near the fascial point with routine rehabilitation treatment, and a control group undergoing routine rehabilitation treatment. The patients will be followed up for 6 months to observe their hand spasm and limb function after treatment. The study flow chart is shown in Fig. 1. An example template for the content of admission plans, interventions and evaluation recommendations is shown in Fig. 2.

**Fig. 1 Fig1:**
[figure not shown]
Flow chart of the study

**Fig. 2 Fig2:**
[figure not shown]
Example template of recommended content for the schedule, interventions, and assessments

### Ethics

The Ethical Committee of the Seventh People’s Hospital affiliated to Shanghai University of Traditional Chinese Medicine approved the ethical approval of this study on 21 June, 2018 (reference number: 2018-IRBQYYS-012). The research scheme, patient information table and informed consent form were approved by the Ethics Committee. All participants will provide informed consent. The real names of the participants will not appear in the relevant reports of the trial to protect their privacy.

### Study setting

The research objects will be recruited from the Seventh People’s Hospital affiliated to Shanghai University of Traditional Chinese Medicine, Shanghai Second Rehabilitation Hospital and Shanghai Hudong Hospital. Interventions for all patients will be conducted in hospitals where participants are recruited. The Seventh People’s Hospital affiliated to Shanghai University of Traditional Chinese Medicine will be responsible for trial coordination and data management.

### Sample size

Our study will be designed as a randomized controlled trial, and the main outcome is whether hand spasm after stroke is relieved after treatment. Current experience shows that the previous effectiveness rate of conventional acupuncture treatment is about 50%, and the expected effectiveness rate is 85%. The significance test level is 0.05, and the test power is 0.9. Sample size is calculated by using:

$$ \mathit{\mathsf{N}}={\left(\mathit{\mathsf{U}\mathsf{\alpha }}+\mathit{\mathsf{U}\mathsf{\beta }}\right)}^{\mathsf{2}}\times \mathsf{2P}\left(\mathsf{1}-\mathit{\mathsf{P}}\right)/{\left(\mathit{\mathsf{P}\mathsf{1}}-\mathit{\mathsf{P}\mathsf{0}}\right)}^{\mathsf{2}}, $$

where, *N* is the required sample size for each treatment group, and the sample size of each group is equal. When *α* is 0.05 and *β* is 0.1, the normal distribution quantile table shows that:
$$ \mathit{\mathsf{U}\mathsf{\alpha }}\left(\mathsf{0.05}\right)=\mathsf{1.65},\mathsf{and} $$
$$ \mathit{\mathsf{U}\mathsf{\beta }}\left(\mathsf{0.1}\right)=\mathsf{1.28}. $$

*P0* and *P1* represent the original curative effect and the expected curative effect, 50% and 85%, respectively. By substituting the above parameters and values into the formulas, 63 cases will be needed for each group. Accounting for a 10% expulsion rate, the final estimated sample size will be about 70 cases per group (210 in total).

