**Methods/design:**

This multicenter randomized controlled trial will compare the efficacy of fascial-point acupuncture versus sham acupuncture and routine rehabilitation therapy in stroke patients with hand spasm. Patients will be randomized to undergo either the fascial-point acupuncture, the sham acupuncture or the control (routine rehabilitation therapy). We will recruit 210 stroke inpatients who meet the trial criteria and observe the remission of hand spasm and improvement of limb function after 4 weeks of intervention. The first evaluation indices are the remission of hand spasm and the duration of spasm remission. The second evaluation indices are the hand function of the affected limbs and the activities of daily living. When the accumulative total number of cases included reaches 120, a mid-term analysis will be conducted to determine any evidence that experimental intervention does have an advantage.

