### Outcome measures

Therapeutic evaluation will be carried out by the same team member who will be blinded to treatment allocation. The primary evaluation indicators in this study are the hand-spasm score and the duration of spasm relief. The modified Ashworth scale will be used to evaluate the spasm of the hand (mainly including the thumb and the other four fingers) before and after treatment. After the patients have been treated with acupuncture and spasticity relieved, the timing will be started to evaluate the duration of spasticity relieved (during this period, the patient should avoid mental tension, so as not to interfere with the test results).

The secondary evaluation indicators included using electromyography (EMG) to detect the activity of the affected limbs, limb function and activity of daily living evaluation. The modified Ashworth scale will be used to evaluate the degree of hand spasm on the affected side at baseline, 4 weeks after intervention and at 1, 2, 4 and 6 months of follow-up [22]. The modified Ashworth scale was divided into 0, 1, 1^+^, 2, 3 and 4 grades, and was quantified as 0, 1, 2, 3, and 4 and 5 points, respectively (Table 1). Surface EMG will be used to record the changes in surface EMG of the upper limbs on the affected side at baseline and 4 weeks after intervention [23]. The simplified Fugl-Meyer scale will be used to evaluate the upper-limb motor function on the affected side and the modified Barthel Index will be used to evaluate activities of daily living at baseline, 4 weeks after intervention and at 1, 2, 4 and 6 months of follow-up [24, 25]. All measurements will be recorded in the data center.

**Table 1 Tab1:** Modified Ashworth scale

Grade	Assessment standard	Score
0	No increase in muscle tension	0
1	Muscle tension is increased slightly. When the affected part is passively flexed and stretched, it suddenly becomes stuck at the end of joint activity and then presents minimum resistance or release	1
1^+^	Muscle tension is increased slightly. Suddenly stuck in passive flexion and extension occurs within the last 50% of the range of ROM, and then shows minimal resistance	2
2	Muscle tension is increased significantly. Muscle tension of the affected limbs in passive motion increases significantly in most ROM ranges, but still easy to move	3
3	Muscle tension is increased severely. The affected limb’s passive movement has resistance over the whole ROM, so it is difficult to move	4

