### Data analysis

#### Statistical analysis

Statistical analysis of research data will be performed by health statisticians and major researchers using SPSS or SAS. Pearson’s *χ*2 test or Fisher’s exact test will be used to analyze classified variables and continuous variables will be evaluated using Student’s *t* test or an appropriate non-parametric method. All statistical tests will be double-sided. The statistical significance level will be set at 5%. The measured data will be described by mean ± standard deviation. Before the analysis, the normality test and homogeneity test of variance will be carried out. If the normal distribution is satisfied, a *t* test will be used. The LSD or SNK method will be used for multiple comparisons, and the rank sum test will be used for non-normality or non-uniformity of variance.

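### The stated 90% power is for a yes/no relief rate against conventional acupuncture, which is neither the primary endpoint in Outcome measures nor a comparison between the trial's arms

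*Protocol article*

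**What the plan says.** **Sizing.** The Sample size section says that "the main outcome is whether hand spasm after stroke is relieved after treatment". Its rates are given as: "the previous effectiveness rate of conventional acupuncture treatment is about 50%, and the expected effectiveness rate is 85" per cent. It adds: "The significance test level is 0.05, and the test power is 0.9". The result is 63 per group, raised to 70 per group and 210 in total for 10% loss.

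**Primary outcome.** Outcome measures says: "The primary evaluation indicators in this study are the hand-spasm score and the duration of spasm relief". The score is the modified Ashworth grade, coded 0 to 5, taken before and after treatment. The abstract gives the first indices as remission of hand spasm and its duration.

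**Arms.** The abstract, Trial design and Intervention sections describe fascial-point needling plus routine rehabilitation, sham needling beside the point plus routine rehabilitation, and routine rehabilitation alone.

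**Time point.** The abstract plans to "observe the remission of hand spasm and improvement of limb function after 4 weeks of intervention". Outcome measures gives the purpose and schedule of the Ashworth scale as: "evaluate the degree of hand spasm on the affected side at baseline, 4 weeks after intervention and at 1, 2, 4 and 6 months" (the months being follow-up visits).

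**Analysis.** Statistical analysis assigns tests by type of variable (chi-square or Fisher for categorical data, t or rank tests otherwise) and states: "All statistical tests will be double-sided".

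**The concern.** A power statement is useful only if it refers to the endpoint and the contrast on which the trial will be judged. This one misses both.

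- **Endpoint.** The calculation is for a proportion relieved. The primary indicators in Outcome measures are an ordinal score and a time. The article states no Ashworth change that would turn the score into relieved or not relieved.
- **Contrast.** The 50% belongs to a treatment that no patient in the trial is assigned to. No rate is given for sham or for rehabilitation alone, and the section does not say which pair of arms the 90% refers to.

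Two things are at stake. A reader cannot tell what difference the trial was designed to detect. And while one section names a relief rate as the main outcome and another names a score, the headline variable could be chosen after the data are seen.

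**Working it through.** **1. Side by side.**

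| Place | Main or primary outcome | Comparator |
|---|---|---|
| Abstract | remission; duration of remission | sham; routine rehabilitation |
| Sample size | relieved or not | conventional acupuncture, 50% |
| Outcome measures | Ashworth hand score; duration of relief | none named |

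Relief and remission can be read as one concept, so there are two competing versions: a rate and a score. Conventional acupuncture appears only in the sizing row.

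**2. The plan's own figure.** Inputs from the Sample size section: P0 = 0.50, P1 = 0.85, Uα = 1.65, Uβ = 1.28. With P taken as the mean, (0.50 + 0.85)/2 = 0.675:

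N = (1.65 + 1.28)² × 2 × 0.675 × 0.325 / 0.35² = 30.7, so 31 per group.

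With 1.96 in place of 1.65, to match the two-sided testing planned in Statistical analysis, N = 37.6, so 38. Neither is 63. Only the last step reproduces: 63/0.90 = 70, and 3 × 70 = 210. The arithmetic is a separate defect. It matters here because 63 cannot be traced to the stated inputs, so the restated power has to start from 63 as a given.

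**3. If relief is primary.** Take n = 63 per group, two-sided 5%, 85% under acupuncture, comparator rate c and p̄ = (0.85 + c)/2:

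power = Φ{ [ (0.85 − c)√63 − 1.96√(2p̄(1 − p̄)) ] / √(0.85 × 0.15 + c(1 − c)) }

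At c = 0.50: (2.778 − 1.298)/0.614 = 2.41, and Φ(2.41) = 0.992. The other rows follow in the same way.

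| Assumed comparator rate c | Power |
|---|---|
| 40% | above 99.9% |
| 50% | 99% |
| 60% | 89% |
| 70% | 52% |

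The document gives no sham or rehabilitation rate, so the range from 40% to 70% is an assumption, placed on both sides of 50%.

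**4. If the score is primary.** The document gives no expected difference and no SD, so only a standardized difference d can be stated. For 90% power, two-sided 5%, normal approximation:

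d = (1.96 + 1.28) × √(2/63) = 3.24 × 0.178 = 0.58.

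If the 5% is split equally over two primary endpoints, the critical value is 2.24 and d = (2.24 + 1.28) × 0.178 = 0.63.

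**The case against.** **A relief comparison is possible within the plan.** The abstract lists remission as a first index, and Statistical analysis provides a chi-square or Fisher test for categorical variables. This stands: a reader might infer that the power belongs to no test that could be run, and the document does not support that. What remains is that relief is not the primary in Outcome measures, and that the 50% would still describe a treatment that is not given.

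**An article may leave detail to the full protocol or analysis plan.** This holds for the missing relief cut-off and for tying tests to endpoints, so neither counts as a defect by itself. It does not excuse two sections naming different main outcomes, or a control rate that matches no arm.

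**The time point is a slip.** Read literally, Outcome measures places the first Ashworth assessment four weeks after treatment ends, and a reader might infer that there is no end-of-treatment value. But a separate 1-month visit is listed beside it, treatment lasts four weeks, and the same section takes the score before and after treatment. End of treatment is the most plausible meaning, so this is a wording correction.

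**Ashworth under the secondary indicators.** The visit schedule for the scale sits in the secondary paragraph, but the paragraph before it already makes the score primary. This is layout.

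**Duration as a second primary endpoint.** Co-primary endpoints are a legitimate choice, and nothing here requires demoting duration.

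**Conclusion.** The concern holds on two points. The sizing variable (a relief rate) differs from the primary indicators in Outcome measures (a score and a duration), and the 50% control rate belongs to no arm. The stated 90% power therefore describes neither that primary endpoint nor any between-arm comparison in this trial.

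A reader might infer that the trial is too small. The document does not show this. At 63 per group the power for relief runs from above 99.9% to 52% as the assumed sham rate goes from 40% to 70%, with 85% under acupuncture. For the score, 90% power needs a standardized difference of about 0.58, and the document offers nothing to judge whether that is realistic. These figures assume 63 evaluable patients per group, a single two-sided 5% comparison and normal approximations.

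**What to change.** 1. State one primary endpoint, one contrast and one time point in the same terms in the abstract, Sample size and Outcome measures. One example is the modified Ashworth hand score at the end of the four-week treatment, acupuncture against sham.
2. In Outcome measures, reword the first post-baseline assessment so that it falls at the end of the four-week intervention.
3. Restate the power at 63 evaluable per group for that same endpoint.
   - If the score is primary, give an assumed difference and SD, and compare them with the standardized difference of about 0.58 that 63 per group detects with 90% power. A relief rate cannot be used to power the score.
   - If relief is primary, define it by a stated Ashworth change and report power over assumed sham rates on both sides of 50%, as tabulated above.
4. Stop using the conventional-acupuncture rate as the control rate.
5. Whether duration stays co-primary is the sponsor's choice, provided the plan says how the error rate is controlled over the two. An equal split moves the detectable difference from 0.58 to 0.63.

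The cost is amendment wording and one explicit planning assumption. No extra patients or visits are proposed. The power statement becomes conditional on that assumption.

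### The stated formula and inputs give 31 patients per group, not 63, and they use a one-sided quantile although all tests are declared two-sided

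*Protocol article*

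**What the plan says.** The Sample size section of the protocol article sizes the trial on a binary endpoint: "the main outcome is whether hand spasm after stroke is relieved after treatment". It takes 50% as the existing success rate and 85% as the expected one, and adds: "The significance test level is 0.05, and the test power is 0.9". The formula is N = (Uα + Uβ)² × 2P(1 − P) / (P1 − P0)², with Uα = 1.65 and Uβ = 1.28. N "is the required sample size for each treatment group, and the sample size of each group is equal". P without a subscript is not defined.

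The section then reports the result of the substitution as "63 cases will be needed for each group". Allowing for 10% loss, this becomes 70 per group and 210 in total.

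Under Data analysis, the Statistical analysis section sets a 5% significance level and says: "All statistical tests will be double-sided".

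**The concern.** Two things do not fit. The formula and all its numeric inputs are printed, but the answer is not the one they give. And 1.65 is the normal quantile for a one-sided 5% test, while the analysis is two-sided at 5%.

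This paragraph is the only justification the article gives for recruiting 210 patients. If 63 does not follow from 50%, 85%, 5% and 90%, then either a step or an input is wrong, and the stated power does not describe the trial that will be run. A reader cannot tell whether the design targets the printed 35-point difference or a smaller one.

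**Working it through.** **Inputs, all from the Sample size section:** P0 = 0.50, P1 = 0.85, difference 0.35, Uα = 1.65, Uβ = 1.28. **Assumption:** P is the mean of the two rates, (0.50 + 0.85)/2 = 0.675. This is the usual reading, but the article does not state it.

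**1. The plan's own calculation**

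- (1.65 + 1.28)² = 2.93² = 8.5849
- 2 × 0.675 × 0.325 = 0.43875
- 0.35² = 0.1225
- N = 8.5849 × 0.43875 / 0.1225 = **30.75, so 31 per group**

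The stated 63 is not reproduced.

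**2. Can the undefined P rescue it?** P(1 − P) is largest at P = 0.50, so that value gives the ceiling.

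| P | N with Uα = 1.65 | N with Uα = 1.96 |
|---|---|---|
| 0.675 (mean) | 30.75 → 31 | 37.60 → 38 |
| 0.50 (ceiling) | 35.04 → 36 | 42.85 → 43 |
| 0.85 | 17.87 → 18 | 21.85 → 22 |

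No choice of P reaches 63 with either quantile.

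**3. The two-sided quantile.** (1.96 + 1.28)² = 10.4976, and 10.4976 × 0.43875 / 0.1225 = **37.60, so 38 per group**. The mismatch in sidedness moves N from 31 to 38. It is an inconsistency in its own right, but it does not explain 63.

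**4. Other methods tried.** All are two-sided, at 90% power, for 85% against 50%:

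- Two-proportion formula with separate null and alternative variances: 36 per group, or 42 with continuity correction.
- The same at a level of 0.05/3: 46, or 52 with continuity correction.
- The printed formula at 0.05/3: 48.35, so 49 (up to 55.09, so 56, at P = 0.50).
- Three-group chi-square: 37 for rates 85/50/50%, and 46 for rates 85/67.5/50%.

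None gives 63. The nearest figure is double the formula result: 2 × 30.75 = 61.5, so 62. A two-arm total may have been read as a per-arm number, but this is a guess and it misses 63 by one.

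**5. The last step is correct.** 63 / 0.9 = 70, and 3 × 70 = 210. The fault lies before this step.

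**6. What 63 evaluable per group delivers.** For two-sided 5%, using the pooled variance under the null:

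- 0.35 × √63 = 2.778
- 1.96 × √0.43875 = 1.298
- √(0.50 × 0.50 + 0.85 × 0.15) = √0.3775 = 0.6144
- z = (2.778 − 1.298) / 0.6144 = 2.41, so power = **99.2%**

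At a level of 0.05/3, power is 97.4%.

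**7. The effect that matches 63.** Solving the printed formula for N = 63, with P as the mean rate, gives P1 ≈ 0.753 with 1.65 and P1 ≈ 0.778 with 1.96, against 0.50. The direct power calculation reaches 90% at P1 ≈ 0.774 (two-sided). A 63-patient arm therefore has 90% power for about 78% against 50%, a difference of some 28 points, not 35.

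**The case against.** The strongest reply is that the error is conservative. If 50% and 85% are right, 63 exceeds both the one-sided requirement (31) and the two-sided one (38). The planned size then covers two-sided testing even with a three-comparison correction, and no patient number or test has to change. This is correct, and it means the finding is not one of too few patients. It does not make the paragraph true: the printed substitution gives another number, and the stated 90% power is not the power at 63.

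A second reply has more force. The article cannot show whether the arithmetic or an input is wrong. The formula returns 63 at an expected rate of about 75% with the printed quantile. If 75% had been intended, two-sided power at 63 per group would be about 83%, and quoting 99% would mislead. The sponsor must therefore confirm the rates before the power statement is rewritten.

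Third, the 50% is described as the rate for conventional acupuncture, which is none of the three arms; the comparators are sham acupuncture and routine rehabilitation. The power figures also take no account of the mid-term analysis at 120 cases mentioned in the Abstract. They should be read as conditional on 50% in the comparator arm and on a single final test.

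Neither text extraction nor condensing for a journal explains the gap. Formula, inputs and result are all legible, and 63 agrees with the 70 and 210 that follow it.

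**Conclusion.** The point holds. The stated formula and inputs give 31 per group, or 38 with the quantile that matches the declared two-sided tests, against 63 stated: a factor of 2.0 or 1.7. With P left free, the ceilings are 36 and 43, so the conclusion does not depend on taking P as the mean rate.

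The 90% power claim is also wrong for 63 evaluable patients per group. For 85% against 50% at two-sided 5%, the design has more than it claims, about 99%. This rests on the printed rates applying to the pair of arms compared and on one final test. The sample size and power statement must be corrected as written, although at the stated rates the trial is not underpowered.

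**What to change.** Keep the recruitment target of 70 per group and rewrite the Sample size paragraph:

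1. Confirm that 50% and 85% are the intended rates, and say which arm the 50% stands for.
2. Define P as the mean of P0 and P1.
3. Replace 1.65 with the two-sided 5% quantile, 1.96, to agree with the Statistical analysis section.
4. State that the formula then gives 38 per group for 85% against 50%.
5. State what 63 evaluable per group provides: at two-sided 5%, per pairwise comparison, about 99% power for 85% against 50%, or 90% power for about 78% against 50%.

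If step 1 shows that another expected rate was meant, restate N and the power for that rate in place of the figures in steps 4 and 5.

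With the stated rates confirmed, the cost is wording only, and recruitment does not change.

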### Inclusion criteria

Cerebral hemorrhage or cerebral infarction confirmed by computed tomography (CT) or magnetic resonance imaging (MRI)First onset, unilateral hemiplegiaThe onset time is more than 2 weeks, and the vital signs are stableAge 30–80 yearsThe clinical manifestations are spastic paralysis of the upper limbs, Brunnstrom stages II–IV of the upper limbs and hands with hemiplegiaThe improved Ashworth score of the hand of the hemiplegic side is grade 1^+^ to 3Stable condition, clear consciousness, no aphasia, no intellectual impairment, can understand the content of the scale and cooperate with the examination and treatmentNo sedative or muscle relaxant has been taken in the last 2 weeksPatients have signed an informed consent form

